### Masking {17a}

No masking procedures will be undertaken.

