## Abstract

**Background:**

Rhegmatogenous retinal detachment (RRD) is a potentially blinding condition that affects ~ 1 in 10,000 adults per year. Retinal detachment surgery usually involves internal reapposition of the retina using the injection of a gas tamponade into the vitreous cavity. However, this has downsides including delayed visual recovery, the need to posture postoperatively, limiting fundal view during postoperative monitoring, and the risk of raised intraocular pressure. We examine a novel surgical variation, using a temporary suprachoroidal viscobuckle (SCVB) instead of gas. SCVB involves the controlled injection of high viscosity viscoelastic through an external scleral incision into the suprachoroidal space to create an indent under a causative retinal break. The sodium hyaluronate viscoelastic is resorbed over 2–3 weeks, long enough for intraoperative laser retinopexy to cause chorioretinal adhesion. The primary objective of this study is to establish if it is feasible to recruit, retain, and evaluate patients with RRD into a larger randomised controlled trial of SCVB. Secondary objectives are to make a preliminary assessment of safety and efficacy.

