**Methods:**

This multicentre, randomised, controlled, two-group, unmasked feasibility trial recruits participants with primary RRD and a break or breaks within 1 clock hour. The CE-marked sodium hyaluronate viscobuckle is created during otherwise standard pars plana vitrectomy RRD surgery. Feasibility outcomes include screen failure rate, rate of recruitment, protocol compliance, and participant retention. The main efficacy outcome is retinal attachment with no intravitreal tamponade present and no subretinal fluid which could spread, without the need for further surgery, at week 12. The key secondary efficacy outcome is Early Treatment of Diabetic Retinopathy Study best-corrected visual acuity at week 24. Safety is recorded through adverse events and serious adverse events.

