## Background {6a, 6b}

Rhegmatogenous retinal detachment (RRD) is a potentially blinding condition that occurs when a break in the neurosensory retina allows vitreous fluid to pass into the subretinal space, lifting the neuroretina off the underlying retinal pigment epithelium (RPE). This typically causes a corresponding visual field defect that expands over time to involve the fovea, with loss of central vision. RRD affects ~ 1 in 10,000 adults per year in the United Kingdom (UK) and is the most common indication for retinal surgery [1–3]. Most RRDs require surgical repair, with the most common operation in the UK being vitrectomy, cryotherapy (cryo), or laser retinopexy and intravitreal gas tamponade; the next most frequent is scleral buckling, then combined vitrectomy with scleral buckling [2]. The primary reattachment rate following surgery has been reported as 80–90% [1, 2, 4].

The use of intravitreal expansile gases in RRD repair is burdensome for patients due to the need for head posturing (to maximise tamponade effect across the break) and severely reduces vision whilst the gas fills the eye. The gases take about 2–8 weeks to absorb; during this time, patients cannot fly, are advised not to drive, and must not have general anaesthesia using nitrous oxide which can cause gas expansion. Gases may increase the likelihood of post-vitrectomy cataract and postoperative intraocular pressure (IOP) elevation. Gases obscure the fundal view, making post-operative retinal examination and monitoring difficult.

Scleral buckling is one of the oldest recognised surgical procedures for the treatment of RRD [5]. It involves the suturing of a silicone explant onto the sclera to produce an indentation over the detached retina and retinal breaks [6]. This promotes retinal reattachment when combined with retinopexy to seal the break via a chorioretinal adhesion. Difficult surgical techniques, prolonged recovery and associated complications, i.e. injury to the extraocular muscles and diplopia, distortion of the globe and refractive change, ocular ischaemic syndrome, and exposure of the implant, have meant that surgeons have generally shifted away from this technique [2].

A technique that combines the advantages of vitrectomy and scleral buckling, without the burden of gas tamponade, could materially impact how vitreoretinal surgeons undertake the most commonly performed retinal operation [3].

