### Randomisation {16a, 16b, 16c}

Randomisation and allocation are performed in the operating theatre using the centralised web-based Castor electronic data capture (EDC) system (Amsterdam, Netherlands), after the internal search of the eye and exclusion of additional breaks in the detached retina. Those who were found to have additional breaks will be documented as screen failures. The PI or delegated SI will undertake randomisation, and all have been allocated logins to the VIKING study EDC. Allocation occurs on the web portal immediately and is 1:1 to either SCVB or comparator with no randomisation stratifiers.

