**Fig. 1 Fig1:**
[figure not shown]
Flow chart demonstrating the participant pathway

**Table 1 Tab1:** Schedule of assessments {13}

	Baseline	Surgery	Day 1	Day 10	Week 6	Week 12	Week 24
Visit number	1	2	3	4	5	6	7
Visit window (days)	Day −21 to 0	NA	0	± 3 days	± 14 days	± 14 days	± 30 days
Screening and consent	R						
Demographics and history	R						
Best-corrected visual acuity (ETDRS)	R						R
Snellen visual acuity			x	x	x	x	
Slit lamp examination	x		x	x	x	x	x
Intraocular pressure	x		x	x	x	x	x
Lens grading (phakic eyes only)	R		*	*	*	*	R
Vitrectomy and retinopexy		X					
*Intervention group:* Suprachoroidal hyaluronic acid		R					
*Control group:* Gas tamponade		X					
Conmeds	R	R	R	R	R	R	R
Adverse events	R	R	R	R	R	R	R

*R* research visit, *X *standard of care assessment

*phakic eyes only

Participants will be treated at baseline and followed up in accordance with typical standard of care, on day 1, day 10, week 5, 12, and week 24.

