Intervention {11a}	Surgical treatment of retinal detachment with vitrectomy and SCVB with the licenced high viscosity cohesive preparations of hyaluronic acid OVD (HEALON5™ PRO OVD [Johnson&Johnson], OphteisBio [Rayner], and NuVisc™ PRO [BVI])
Comparator {11a}	Standard vitrectomy with cryotherapy, retinopexy and gas tamponade
Study Duration	24 months
Safety Measures {12}	Adverse events and serious adverse events
Primary Efficacy Measure {12}	Feasibility outcomes: - Screen failure rate - Rate of recruitment - Protocol compliance - Participant retention and discontinuation Main efficacy outcome: Attachment of the retina with no intravitreal tamponade present and no subretinal fluid which could spread, without the need for further surgery, at week 12 Key secondary efficacy outcome: ETDRS best-corrected visual acuity at week 24
Number of Study Sites {9}	6 National Health Service (NHS) University Hospitals

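### Masking is ruled out for everyone, including the week-24 ETDRS acuity examiner, who in most eyes without a re-operation could have been kept unaware of the arm

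*Protocol article*

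**What the plan says.** The section Masking {17a} is one sentence: "No masking procedures will be undertaken". It names no role or visit and gives no reason. The abstract agrees: "This multicentre, randomised, controlled, two-group, unmasked feasibility trial recruits participants with primary RRD".

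Appendix Table 3 lists "Key secondary efficacy outcome: ETDRS best-corrected visual acuity at week 24". Table 1 (Schedule of visits {13}) marks ETDRS acuity as a research assessment at baseline and week 24 only, with a ±30-day window at week 24. The visits in between use Snellen acuity.

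On how long each agent stays in the eye, Background {6a, 6b} says "The gases take about 2–8 weeks to absorb", and the abstract says "The sodium hyaluronate viscoelastic is resorbed over 2–3 weeks".

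On who knows the arm, Randomisation {16a, 16b, 16c} says "The PI or delegated SI will undertake randomisation, and all have been allocated logins to the VIKING study EDC". The article does not say who performs refraction or ETDRS testing at week 24.

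Statistical analysis {14, 20a, 20b, 20c} plans descriptive results only. It justifies 25 per arm partly by the need to estimate acuity variance, and it lists the effect-size estimate among the considerations for going on to a pivotal trial. Objectives {7} makes a preliminary look at efficacy a secondary objective and expects the next trial to be a non-inferiority trial covering anatomic and visual outcome. Trial status gives 1 June 2025 as the completion date.

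**The concern.** An open design is understandable for the surgeon, who performs the procedure, and for the participant, who experiences the gas. It does not follow that every outcome assessor must also know the arm. ETDRS BCVA depends on how the refraction is done, how hard the patient is pressed to guess, and how letters are scored. An examiner who knows the allocation can influence all three without meaning to.

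At stake is the between-arm acuity estimate. It will not be tested here, but it is one input to the decision on a pivotal trial and to that trial's design. The study also sets out to learn whether patients can be evaluated. Excluding all masking gives up the chance to learn whether examiner-masked acuity testing works across six sites.

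**Working it through.** **Plan's own figure.** The article gives no number for masking, and no acuity SD or margin. Its one precision statement, ±11% around an 80% evaluable proportion with n = 50, reproduces: 1.96 × √(0.8 × 0.2 / 50) = 0.111. It does not bear on this point.

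**Step 1. Could the eye reveal the arm at week 24?** Inputs are the week-24 visit with its ±30-day window (Table 1), gas absorption of up to about 8 weeks (Background) and viscobuckle resorption of up to 3 weeks (abstract). Days are counted from surgery.
- Earliest visit: 24 × 7 − 30 = 168 − 30 = day 138.
- Latest stated gas absorption: 8 × 7 = day 56. Margin: 138 − 56 = 82 days.
- Latest stated viscobuckle resorption: 3 × 7 = day 21. Margin: 138 − 21 = 117 days.

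After a single uncomplicated operation, neither agent should remain at any point in the window.

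**Step 2. Which eyes are exceptions?** Consent {11b, 26a} puts surgical failure at about 10–20%, and Concomitant care {11d} offers standard vitrectomy for re-detachment. Applied to 50 participants, that is 5 to 10 eyes. If the re-operation uses gas that clears within 56 days, only eyes re-operated after day 138 − 56 = 82 could still hold gas at the earliest visit. For a visit on day 168 the cut-off is day 168 − 56 = 112. Exceptions exist but should be a minority.

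**Step 3. Which statistic is exposed?** If the examiner adds a constant c letters to every result in one arm, that arm's mean moves by c. Its standard deviation does not change, because SD(X + c) = SD(X). The acuity variance, which the article gives as a reason for 25 per arm, is not harmed by this mechanism. The difference between arms is.

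**Step 4. How large might it be?** The documents give neither a bias nor an SD, so this is illustration only. Assume a shift of 2–5 letters and an SD of 10–20 letters, with 25 per arm. The standard error (SE) of the difference is SD × √(2/25).

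| Assumed SD (letters) | SE of difference | 95% half-width (1.96 × SE) | 2-letter shift / SE | 5-letter shift / SE |
|---|---|---|---|---|
| 10 | 2.83 | 5.54 | 0.71 | 1.77 |
| 15 | 4.24 | 8.32 | 0.47 | 1.18 |
| 20 | 5.66 | 11.09 | 0.35 | 0.88 |

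The assumed shift runs from 0.35 to 1.8 SE. It is inside the 95% half-width in every row, but not plainly negligible.

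**The case against.** The best defence is that nothing here is an error. The open design is declared consistently, the primary objective is feasibility, no comparison is planned, and neither feasibility threshold in Table 2 uses acuity. That is correct, and it limits the weight of the point. It does not remove it, because a descriptive between-arm estimate still informs the next trial.

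The defence also has practical arguments, and these stand:
- Gas is not the only way the arm can become known. A reader might infer from the timing that it is, but participants know what they had, site records show it, and adverse events and medications are collected at the same visit. Lens status may also give a hint, since the article expects possibly fewer cataracts with the viscobuckle.
- Some re-operated eyes may hold tamponade at week 24.
- A reader might assume that masking needs no extra staff. The article does not say who tests acuity, so this cannot be established. If the tester is the operating surgeon, or someone who works from the operation note, a second person is needed.
- Masking the examiner does nothing about the effort of a participant who knows the arm.
- With data collection over, a change of wording cannot alter this trial's measurements.

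These arguments support a qualified remedy. None of them is a reason why an examiner who could be kept unaware should be told the arm.

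**Conclusion.** The point holds as a modest, low-cost design improvement. The blanket exclusion of masking leaves the week-24 between-arm BCVA estimate open to examiner bias that could have been avoided in most eyes without a re-operation. The margin is 82 days for gas and 117 days for the viscobuckle, taking the article's absorption times at face value and counting from surgery.

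Two stronger readings are tempting and are not supported. One is that the acuity SD handed to the pivotal trial is corrupted. A constant shift leaves it unchanged. The other is that the bias favours the viscobuckle by a known number of letters. The documents give neither direction nor size, and the 0.35 to 1.8 SE range rests wholly on assumed values. No planned test, feasibility threshold or sample-size figure changes.

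**What to change.** Reword Masking {17a} along these lines: surgeons and participants are unmasked; where existing site staffing allows, the person who performs refraction and ETDRS BCVA at week 24 is not the operating surgeon and is not shown the allocation or the operation note; participants are asked not to disclose their arm to that person. Add one case report form item recording whether the examiner knew the arm, and report the answers as a feasibility result.

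Since the trial is complete, three actions remain open to the sponsor. Report who measured week-24 BCVA at each site and whether they knew the arm. Attach a caveat to the between-arm acuity estimate. Carry examiner masking, with the recording item, into the pivotal design.

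Cost: a site instruction and one form item, with no change to visits, sample size or treatment. Some unmasking through participants, records or re-operated eyes should be expected, and the form item would record it. Where a site has no unaware staff member, the assessment stays unmasked and is reported as such.

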### Schedule of visits {13}

The patient flow is shown in Fig. 1, with the schedule of procedures by visit in Table 1.

**Fig. 1 Fig1:**
[figure not shown]
Flow chart demonstrating the participant pathway

**Table 1 Tab1:** Schedule of assessments {13}

	Baseline	Surgery	Day 1	Day 10	Week 6	Week 12	Week 24
Visit number	1	2	3	4	5	6	7
Visit window (days)	Day −21 to 0	NA	0	± 3 days	± 14 days	± 14 days	± 30 days
Screening and consent	R						
Demographics and history	R						
Best-corrected visual acuity (ETDRS)	R						R
Snellen visual acuity			x	x	x	x	
Slit lamp examination	x		x	x	x	x	x
Intraocular pressure	x		x	x	x	x	x
Lens grading (phakic eyes only)	R		*	*	*	*	R
Vitrectomy and retinopexy		X					
*Intervention group:* Suprachoroidal hyaluronic acid		R					
*Control group:* Gas tamponade		X					
Conmeds	R	R	R	R	R	R	R
Adverse events	R	R	R	R	R	R	R

*R* research visit, *X *standard of care assessment

*phakic eyes only

Participants will be treated at baseline and followed up in accordance with typical standard of care, on day 1, day 10, week 5, 12, and week 24.

### Recruitment {15}

Participants will be recruited from NHS outpatient clinics, having been referred from general practitioner (GP) surgeries, community optometrists and other ophthalmologists. The estimated duration of recruitment is 24 months.

Participants will be recruited from the day of presentation. The examining surgeon and/or research nurse will identify and approach patients for consent.

### Statistical analysis {14, 20a, 20b, 20c}

VIKING is not powered to test an efficacy-based hypothesis and no interim analysis is planned. The results will instead be descriptive, without any statistical comparisons. As noted in the section above, this study is not designed to test a hypothesis, but rather to inform a future study. We selected 25 participants for each arm, as that will give an estimate of visual acuity variance and may start to expose any difference in anatomic success rate [22, 23].

A total of 50 patients will provide a reasonable estimate of screening success, recruitment rate, retention, the ability to evaluate patients, attrition and time to ‘stress test’ the protocol, addressing the main feasibility outcomes of the study. With a sample size of 50 participants, we will be able to estimate the proportion of participants with an evaluable primary outcome of 80% with a 95% confidence interval of ± 11%.

From a feasibility perspective, we anticipate that a pivotal trial would be deliverable if the criteria detailed in Table 2 were met.

We recognise that the decision to proceed with a subsequent pivotal trial depends on an appreciation of the totality of the results, not just the feasibility metrics, including the apparent risks, benefits, estimated effect size, minimum clinically important difference, future unmet need, suitable funding streams, input from patient focus groups, amongst other factors (Table 2).

**Table 2 Tab2:** Feasibility thresholds for a future study

Feasibility metric	No-go	Protocol modifications	Proceed without change
Recruitment (patients per month per site)	< 0.1*	0.1–0.3	> 0.3
Evaluable primary outcome (combining attrition and otherwise missing primary outcome data)	80%	81–88%	> 88%

*A slowly recruiting trial may be justified if the sample size is deliverable, and the clinical impact warrants an extended recruitment timeline and/or a large number of sites

A description of baseline demographics and ocular characteristics will be provided by group to include age, sex, best-corrected visual acuity (BCVA), laterality, lens status, location, and number of retinal breaks, and RD location.

The efficacy population will be ‘intent-to-treat’, including all randomised participants, but a ‘per protocol’ analysis will include all those randomised to SCVB who received it, and all those randomised to standard vitrectomy who received it.

For continuous efficacy variables, we plan to report the mean and standard deviation, unless the data appear skewed, in which case we will consider reporting the median and interquartile range. For categorical values, we will report proportions, with 95% confidence intervals.

In addition to the main BCVA results, BCVA will be reported in the subgroups of eyes that are phakic and pseudophakic, and those with macular-on and macular-off RDs, since post-vitrectomy cataract and macular status can materially influence BCVA outcomes.

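### The trial's size rests partly on estimating visual acuity variance, but the skewness rule lets the SD go unreported; the SD should always be given, with the residual SD beside it

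*Protocol article*

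**What the plan says.** All of the key text is in the Protocol article under Statistical analysis {14, 20a, 20b, 20c}.

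- On size: "We selected 25 participants for each arm, as that will give an estimate of visual acuity variance". A possible early signal on anatomic success is given as a further reason.
- On summaries: "For continuous efficacy variables, we plan to report the mean and standard deviation, unless the data appear skewed", and then "in which case we will consider reporting the median and interquartile range".
- On purpose: "The results will instead be descriptive, without any statistical comparisons". The study is meant to inform a later one.
- On prognostic factors: BCVA is also to be shown by lens status and by macular status, "since post-vitrectomy cataract and macular status can materially influence BCVA outcomes".

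The abstract states: "The key secondary efficacy outcome is Early Treatment of Diabetic Retinopathy Study best-corrected visual acuity at week 24". Table 1 schedules ETDRS BCVA at baseline and at week 24. Allocation "is 1:1 to either SCVB or comparator with no randomisation stratifiers". The article states no SD, baseline correlation or margin for BCVA.

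**The concern.** One stated reason for the sample size and the stated reporting rule do not fit together. If the trial is sized partly to learn how variable acuity is, the SD has to appear in the report whatever the shape of the data. As written, an analyst who finds skewed acuity can report only a median and IQR and still be following the plan.

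Skewness is a realistic prospect. The Consent section puts the failure rate of this surgery at about 10–20%, the efficacy population keeps everyone randomised, and the plan itself expects cataract and macular status to move acuity. A lower tail of poor results is plausible, and an IQR largely ignores such a tail.

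What is at stake is the planning of the next trial. The Objectives section expects a non-inferiority design whose hypothesis covers anatomic or visual outcome. If BCVA is used to size it, a variance inferred from an IQR could make it too small. If its analysis adjusts for baseline, a raw SD alone would make it larger than necessary.

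**Working it through.** **1. The plan's own precision figure.** The article states: "we will be able to estimate the proportion of participants with an evaluable primary outcome of 80% with a 95% confidence interval of ± 11" percentage points. Check: 1.96 × √(0.8 × 0.2 / 50) = 0.111, or 11.1 points. It reproduces, but it concerns the evaluable proportion. No precision is stated for the BCVA variance.

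**2. Precision of the SD at the planned size.** The 95% limits, as multiples of the estimated SD, are √(df/χ²₀.₉₇₅) and √(df/χ²₀.₀₂₅).

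| Basis | df | SD limits | Variance limits |
|---|---|---|---|
| One arm, 25 eyes | 24 | 0.78 to 1.39 | 0.61 to 1.94 |
| Pooled within arm, 50 eyes | 48 | 0.83 to 1.25 | 0.70 to 1.56 |
| One arm, 20 eyes (80% of 25 evaluable) | 19 | 0.76 to 1.46 | 0.58 to 2.13 |

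These limits assume normal data, and pooling assumes similar variance in the two arms.

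**3. What is lost if only the IQR appears.** A reader would recover an SD as IQR/1.349, which is right for normal data. Two assumed left-skewed letter scores, simulated and held within 0 to 100:

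- Mixture of 88% with mean 78 and SD 8, and 12% with mean 45 and SD 20. True SD 14.7, recovered SD 9.3. Unrounded variance ratio 2.5.
- 85 minus an exponential variable with mean 15. True SD 14.7, recovered SD 12.2. Variance ratio (14.66/12.21)² = 1.44.

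For a comparison of means, required size is proportional to variance. The recovered value would therefore give about 1/2.5 = 40% of the required number in the first case and 1/1.44 = 69% in the second.

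**4. Raw against adjusted variance.** Adjusting for baseline multiplies the variance by 1 − r², where r is the baseline to week-24 correlation. As an illustration only, assume SD 15 letters, margin 5 letters, one-sided 0.025 and 90% power. Unadjusted n per arm = 2 × (1.960 + 1.282)² × 15² / 5², which rounds up to 190.

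| Assumed r | 1 − r² | n per arm |
|---|---|---|
| 0 (unadjusted) | 1.00 | 190 |
| 0.2 | 0.96 | 182 |
| 0.3 | 0.91 | 173 |
| 0.5 | 0.75 | 142 |
| 0.7 | 0.51 | 97 |

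**5. Macular status.** If a share w of eyes is in one macular group, the groups differ by d letters and the within-group SD is s, then raw variance / within-group variance = 1 + w(1 − w)d²/s². With assumed w of 0.3 to 0.5, d of 10 to 20 and s of 10 to 20:

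- lowest (w 0.3, d 10, s 20): 1 + 0.21 × 100/400 = 1.05
- highest (w 0.5, d 20, s 10): 1 + 0.25 × 400/100 = 2.0

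Steps 4 and 5 probably overlap, since macula-off eyes tend to start with poor acuity. The two effects should not be multiplied together.

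**The case against.** The strongest reply is that the default does deliver the SD, that the skewness clause only says a median and IQR will be considered, and that the investigators keep the dataset and can compute any variance later. All of that is true. It makes the gap one of wording and reporting, not a loss of information. It does not remove the mismatch: the article chose to state the rule, and the rule does not protect a quantity that the size was chosen for. Others planning a similar trial would have only the published summary, because the article says the datasets will not be publicly available.

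A reader might go further and infer that the raw SD is the wrong variance for a pivotal trial. The documents do not support that. No section fixes the later analysis as baseline-adjusted or makes BCVA its primary endpoint, and the main efficacy outcome here is binary attachment. The raw SD is correct for an unadjusted comparison and errs on the safe side for an adjusted one.

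A reader might also object that the plan ignores macular and lens status, or should compare the arms with adjustment. It does report BCVA within those subgroups, which gives part of the within-group picture. It also deliberately makes no statistical comparisons, so chance imbalance under unstratified allocation matters less here. A residual SD is an addition that an analysis plan may already contain; its absence from the article is not an error.

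**Conclusion.** The point holds in a limited form. The article justifies 25 per arm partly by estimating acuity variance, then allows a summary that need not contain it. Whether this happens depends on how the data look and on a discretionary choice.

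If the SD were omitted, a variance back-calculated from the IQR could be too low by a factor of about 1.4 to 2.5 in the two assumed distributions. If the SD is reported and the later trial adjusts for baseline, the raw figure is conservative: the adjusted variance would be 96% to 51% of it for an assumed correlation of 0.2 to 0.7. At the low end of that range the gain is trivial; at the high end it roughly halves the trial. The documents give no acuity SD, correlation, macular gap or margin, so every such input here is an assumption. Only the SD limits follow from the planned numbers alone, given normal data.

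**What to change.** Replace the skewness rule for BCVA with a commitment to the following:

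1. Always report the week-24 ETDRS BCVA SD, per arm and pooled within arm, with its 95% CI. Add the median and IQR if the data are skewed. In that case use a bootstrap interval, because the chi-square limits rely on normality.
2. Report the correlation between baseline and week-24 ETDRS BCVA.
3. Fit one model over both arms with arm, baseline BCVA, macular status and baseline lens status, and report the residual SD with its 95% CI. With all 50 eyes this leaves 50 − 5 = 45 degrees of freedom, so the limits are about 0.83 to 1.26 times the estimate.
4. Present the raw and residual SDs side by side as planning inputs, so that the later trial can use whichever matches its analysis.

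An adjusted mean difference with a CI is optional, since the trial is descriptive. The Trial status section says the study is complete and results are due in 2026, so the change belongs in the analysis and results report. It needs no new data and costs one extra model and a few lines in a table.
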